### Interim analyses {21b}

N/a no interim analyses are planned due to the minimal risks of the trial.

### Methods for additional analyses (e.g., subgroup analyses) {20b}

N/a. No additional analyses are currently planned.

### Methods in analysis to handle protocol non-adherence and any statistical methods to handle missing data {20c}

Reasons for trial discontinuation will be noted for each randomization group and the reasons will be analyzed for dependence from the randomization group and fabrication mode of the splint. Imputation of missing data is not planned; if unexpectedly a larger number of participants drops out during the trial, further participants will be enrolled to obtain the intended number of participants required for a statistical power of 90%.

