### Criteria for discontinuing or modifying allocated interventions {11b}

Criteria for discontinuing or modifying allocated interventions for a given trial participant are the occurrence of exclusion criteria for the respective cohort or the withdrawal of consent. Interventions may also be discontinued if a participant unexpectedly experiences a worsening of symptoms that the participant considers intolerable.

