### Sample size {14}

The sample size was calculated based on results reported for the OHIP-G14. According to the results of Alajbeg et al. [29], an OHIP-G14 score of 25.29 (SD 12.38) can be assumed for TMD patients. If the non-inferiority margin is set at 5 and a standard deviation of the differences of 10 is assumed, 38 participants are required for the trial with a two-sided paired t-test and a power of 90% on a 5% significance level. As both cohorts can be analyzed together for the primary outcome parameter OHIP-G14, the target number of cases is set at 20 participants per cohort, resulting in 40 participants in total.

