### Plans to promote participant retention and complete follow-up {18b}

Participants are informed about the importance of their adherence and are motivated to follow trial guidelines. Further, participants receive the two splints for free to promote participant retention and complete follow-up. If a participant drops out of the trial or deviates from intervention protocols, the reason for discontinuation and deviation from the protocol will be recorded and it will be assessed on an individual basis if and how data generated during the trial can be implemented in statistical analysis.

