## Statistical methods

### Statistical methods for primary and secondary outcomes {20a}

Absolute and relative frequencies are calculated for binary or categorical variables. For continuous data, the median, mean and standard deviation are specified. In addition, 95% confidence intervals are calculated. The calculations are performed per group (milled and 3D printed) and per cohort (bruxism and TMD). Cross-over effects are examined in all analyses. For the primary outcome parameter OHIP-G14, the group differences are estimated and tested using a linear regression model with corresponding two-sided 95% confidence intervals. The model will include the difference in OHIP-G14 values (milled vs. 3D printed) as a dependent variable and the sequence of the splints and the cohort (bruxism and TMD) as independent variables.

The one-sided test for non-inferiority of 3D printed versus milled splints at the 2.5% significance level is based on the two-sided 95% confidence interval of the linear regression model. The null hypothesis is rejected if the lower limit of the confidence interval for the difference (conventionally milled vs. 3D printed) is above − 5. The same applies to secondary outcomes, namely volume loss of the splint/opposing dentition, pain reduction, jaw mobility, and splint fracture rates.

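### Outcome-related stopping, a pairs-only primary model, no imputation with top-up enrolment, and case-by-case use of dropouts' data can together bias the test towards non-inferiority

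*Protocol article*

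**What the plan says.** Five sections of the protocol article bear on this point.

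- **Stopping {11b}:** "Criteria for discontinuing or modifying allocated interventions for a given trial participant are the occurrence of exclusion criteria for the respective cohort", or withdrawal of consent. A stop is also permitted when a participant finds an unexpected worsening of symptoms intolerable.
- **Eligibility {10}:** in the TMD cohort, GCPS grade III or IV is an exclusion criterion. The GCPS is also completed by this cohort at every visit from T1 to T5, and its component scores are secondary outcomes {12}.
- **Primary model {20a}:** "The model will include the difference in OHIP-G14 values (milled vs. 3D printed) as a dependent variable", with sequence and cohort as covariates. "The one-sided test for non-inferiority of 3D printed versus milled splints at the 2.5% significance level" is read from the two-sided 95% interval, whose lower limit must lie above −5.
- **Missing data {20c}:** "Imputation of missing data is not planned; if unexpectedly a larger number of participants drops out during the trial, further participants will be enrolled", up to the number needed for 90% power. Reasons for discontinuation are recorded and compared by sequence group and by type of splint.
- **Retention {18b}:** for participants who drop out or deviate from the protocol, "it will be assessed on an individual basis if and how data generated during the trial can be implemented in statistical analysis".

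On blinding {17a}, participants and the statistician are blinded and the treating dentists are not.

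**The concern.** Each provision is common in small crossover trials. The difficulty is how they combine. A participant whose pain reaches GCPS grade III on the first splint meets a ground for discontinuation. If that participant leaves, there is no score on the second splint, no difference to enter in the model, and nothing imputed. If enough participants leave, new ones are enrolled, and they count only if they provide values on both splints. The analysed pairs then come from people who managed on both splints.

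In a superiority trial, selection of this kind would often be conservative. Here it is not. If the printed splint really is worse, more participants do badly on it, so removing bad results removes more of the evidence against it and moves the estimate towards zero. Top-up enrolment recovers precision around an estimate that has already shifted. A claim of non-inferiority could therefore be made too readily. Because section {18b} sets no rule and states no blinding for the inclusion decisions, the reader of the results could not tell how far this had happened.

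**Working it through.** **1. Does the text allow poor results to leave the pairs?** Sections {11b} and {10} together make GCPS grade III or IV during follow-up a ground for discontinuing or modifying treatment in the TMD cohort. Section {20a} needs a value on both splints. A participant who leaves during the first splint has none on the second. A participant who stops the second splint after its 2-week visit has a 2-week pair but no 3-month pair. So some losses are certain to drop out of the model and others depend on the decision under {18b}.

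**2. Inputs.** "If the non-inferiority margin is set at 5 and a standard deviation of the differences of 10 is assumed" (section {14}); planned number "resulting in 40 participants in total"; one-sided 2.5% test {20a}. Write d = milled − printed, with a higher OHIP-G14 taken as worse, so d = −5 means printed is worse by exactly the margin.

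**3. The plan's own figure.** The plan states "38 participants are required for the trial with a two-sided paired t-test and a power of 90% on a 5% significance level". With n = [SD × (z₀.₉₇₅ + z₀.₉₀) / margin]² = [10 × (1.960 + 1.282) / 5]² = 42.03, 43 pairs are needed, or 44 with the t distribution. The stated 38 does not reproduce: 38 pairs give 85.1% power and 40 give 86.9%. This is a separate matter, but it means that the top-up target in {20c}, tied to 90% power, rests on a number that gives about 85%.

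**4. Error with outcome-related stopping (assumed).** Simulation of 40 complete pairs, SD of differences 10, true d = −5, within-person correlation 0.3 to 0.7. The worst-scoring participants are removed and enrolment continues until 40 pairs are complete. Entries are the chance of declaring non-inferiority; the nominal value is 2.5%.

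| Assumed dropout | Unrelated to outcome | Same rule on both splints | Stopping on printed only |
|---|---|---|---|
| 5% | 2.5–2.7% | 3.7–4.4% | 4.6–5.7% |
| 10% | 2.4–2.6% | 4.5–6.3% | 7.1–11.3% |
| 20% | 2.5–2.6% | 6.0–10.8% | 13.4–28.0% |

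Under the same rule on both splints, the completers' mean moves from −5.0 to between −4.6 and −4.8 at 5% dropout, and to between −4.4 and −4.6 at 10%.

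**5. An extreme version, by hand.** Suppose everyone with d below −20 stops. The cut is (−20 + 5)/10 = −1.5 SD, which removes 6.7%. The mean of the rest is −5 + 10 × 0.1295/0.9332 = −3.6, with SD about 8.8. With n = 40 the standard error is 8.8/√40 = 1.39, so the shift of 1.39 is about one standard error and the error rises to about 15%. If the cut is at −25 (2.3% removed), it is about 5%. If 6.7% stop but the trigger only correlates 0.3, 0.5 or 0.7 with d, the error is about 4%, 6% or 9%.

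**6. When the splints are equal.** With true d = 0 and the same rule on both splints, the mean bias is about zero. Non-inferiority is declared in 89–94% of trials instead of about 87%, because trimming narrows the spread.

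**The case against.** The strongest reply is that the text is softer than it first appears, and much of this stands.

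- A reader might infer that the test *is* biased. The documents do not support that: they give no dropout rate, and they give no reason to expect more failures on printed splints, since both splints come from one digital design {6b}. Random dropout does no harm, and more stopping on milled splints would bias against the printed ones.
- A reader might infer that staff who know the splint type decide whose data count. Section {18b} names nobody. What can be said is that no blinding of the decision is stated and that the treating dentists are unblinded.
- A reader might infer that dropouts are substituted one for one. Section {20c} describes further enrolment, and only if an undefined larger number drops out.
- A reader might infer that poor responders must be withdrawn. Section {11b} speaks of discontinuing *or modifying*, makes stopping for intolerable worsening optional, and nowhere says that data collection ends.
- A reader might treat any painful DC/TMD diagnosis as a trigger in the bruxism cohort. The criterion also requires orofacial pain as the chief complaint, and no follow-up DC/TMD examination or GCPS is scheduled for that cohort.
- A reader might quote 15% as the expected size. The arithmetic is right, but it assumes stopping only for poor printed results and a trigger identical to the OHIP-G14 difference. The stated triggers are pain grade, exclusion diagnoses and intolerable symptoms.

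The comparison of stopping reasons by splint type in {20c} is a genuine safeguard. However, with about 40 participants and few stops it has little power, and it can reveal the bias without correcting it.

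It could also be said that analysis sets belong in the analysis plan. That would answer silence. Here the article itself fixes the paired outcome, the absence of imputation, the top-up and the individual decisions.

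**Conclusion.** The concern holds in conditional form. As written, the plan can bias the primary test towards non-inferiority if stopping is related to outcome. With the printed splint truly worse by the margin, one-sided error goes from 2.5% to about 4–6% at 5–10% dropout under one stopping rule for both splints, and to about 5–11% if stopping occurs only on printed splints. About 15% is a worst case for a stopping rate near 7%. The 20% row of the table goes higher, but nothing in the article points to losses of that order.

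These sizes rest on assumed dropout rates, on the plan's SD of 10, on correlations of 0.3 to 0.7, and on the worst scores being the ones removed. The shift in the mean comes from the removal, so it arises with or without top-up enrolment. The weakness should be repaired, because the plan contains nothing that corrects the shift if it occurs and section {20b} plans no additional analyses. Whether the stopping criteria are clinically appropriate is not at issue.

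**What to change.** Leave the clinical stopping criteria unchanged and amend the following.

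1. **Sections {18b} and {20c}:** state that after a splint is discontinued, OHIP-G14 is still collected at the stop and at the scheduled visits.
2. **Section {20a}:** include in the primary analysis all randomised participants with any post-incorporation OHIP-G14, in their assigned sequence, using a period-level mixed model with participant as a random effect and treatment, period and cohort as fixed effects. Participants with data on one splint then contribute. Late enrolees are counted in addition to those who dropped out.
3. **Section {18b}:** replace the individual decision with an inclusion rule written in advance and applied blind to splint type.
4. **Supportive sensitivity analysis:** give an unfavourable score to splint-related stops that lack a 3-month value, and report the result beside the primary one. This is needed because the mixed model alone assumes that missing values are predictable from the observed ones. It need not decide the conclusion.

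The cost is revised wording and a few extra questionnaires. The interval may be slightly wider and the result somewhat less favourable to the printed splint.

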### Plans to give access to the full protocol, participant-level data, and statistical code {31c}

The full protocol approved by the Ethics Committee (in German language) and the anonymized dataset for statistical analysis as well as information concerning the statistical analysis can be obtained from the corresponding author on reasonable request.

## Oversight and monitoring

### Composition of the coordinating center and trial steering committee {5d}

N/a since all work related to the trial—enrolling and treating participants, fabrication of splints, and data analysis—is performed at the Department of Prosthetic Dentistry, Center for Dental Medicine, Medical Center, University of Freiburg, Germany. A coordinating center and trial steering committee were not planned due to the monocentric character of the trial and its low risks for the participants.

### Composition of the data monitoring committee, its role and reporting structure {21a}

N/a because a data monitoring committee was deemed not necessary since this clinical trial involves only the use of established and approved materials within their intended purpose, therefore, risks for participants can be regarded as minimal.

### Adverse event reporting and harms {22}

In the time between the incorporation of the first splint and the 6 months control, adverse events and serious adverse events as defined in the Medical Device Regulation (MDR) Article 2, points 57 and 58 are recorded by the trial´s personnel and are assessed for a causal relationship with the applied milled and 3D printed materials. Further, device deficiency (MDR, Article 2, point 59) will be noted in the aforementioned time frame. However, since no additional invasive and/or burdensome procedures are included in the trial, the trial represents an “other clinical investigation” according to German law (Section 64(4) Medizinproduktedurchführungsgesetz (MDPG)). Therefore, (serious) adverse events and device deficiency do not have to be reported to the federal higher authority.

The Ethics Committee of the Albert-Ludwigs-University, Freiburg, Germany will be informed about potential serious adverse events with assumed causal relationship to the clinical trial. Since the investigational materials have CE marking, are processed as suggested by the manufacturers, and are used within the intended purpose, (serious) adverse events are not expected during the trial.

### Frequency and plans for auditing trial conduct {23}

N/a since no audit from an independent party is planned in this Investigator Initiated Trial. The clinical trial will be closely monitored by the trial’s personnel and persons involved in participant treatment will meet regularly to discuss the trial’s progress and potential issues arising during the trial.

### Plans for communicating important protocol amendments to relevant parties (e.g. trial participants, ethical committees) {25}

Protocol amendments will be submitted for review to the Ethics Committee of the Albert-Ludwigs-University, Freiburg, Germany, and will only be implemented in the trial after approval. Entries in trial registries will be updated accordingly and—if trial participants are affected by the amendment—they are informed personally.

### Dissemination plans {31a}

Data will be disseminated through peer-reviewed scientific journals and at clinical and academic conferences. No publication restrictions exist.

## Discussion

3D printing is becoming increasingly popular in dentistry as more complex geometries can be produced with better cost and time efficiency compared to the established milling procedure. Due to these production-specific advantages of 3D printing, a growing number of stabilization splints is fabricated using 3D printing. However, it remains currently unknown whether these 3D printed stabilization splints perform as successfully clinically as milled splints.

The presented trial, therefore, investigates the non-inferiority of 3D printed stabilization splints compared to milled counterparts in terms of OHRQoL, treatment efficacy, and technical result in a monocentric prospective randomized single-blinded crossover trial with a bruxism and a TMD cohort. It was decided to apply a cross-over design to allow for direct comparison of treatment effects of milled and 3D printed splints on the same individual which can be assumed as more precise than a parallel design in this setting [33]. To reduce the carry-over-effects typical for cross-over designs, two arms with different treatment sequences are investigated per cohort, participants are blinded and cross-over effects will be examined in all analyses [33, 34].

Clinical outcomes of the splints are investigated in a bruxism and TMD cohort, since both conditions can be managed by stabilization splints. Bruxism and TMD show large inter-individual variation due to their multifactorial biopsychosocial genesis [15]. There is thus a continuum spectrum for bruxism ranging from physiologic motor action regarded as self-protective behavior of which patients are often unaware to severely destructive bruxism resulting in serious orofacial health problems and tooth decay [8, 9, 35, 36]. Bruxism can further contribute to the genesis of TMD [35, 36] which itself can show symptoms from pain-free TMJ sound to dysfunctional chronic orofacial pain and disability [30]. As a consequence, the definition of bruxism and TMD for trial purposes, which determines participant inclusion and comparability of clinical trials, is challenging. Definitive diagnosis of bruxism requires an instrumental approach using polysomnography including electromyography, which cannot be used routinely in clinical practice or research due to its technical complexity, high cost, and limited availability [5, 37, 36]. Hence, a probable bruxism, referring to bruxism diagnosed by clinical dental examination [5, 37, 36], was set as the inclusion criterion for this trial. For diagnosis of a probable bruxism, different screening instruments have been proposed but no internationally established screening existed at initiating the present trial. Therefore, the authors apply the BSI representing the standard tool applied in Germany for bruxism screening to identify individuals with probable bruxism [36]. The BSI is in many aspects comparable to the BruxScreen developed for setting an international standard in bruxism screening and initially tested by Lobbezoo et al. [35] when the present trial was planned and might thus yield comparable results. Future research comparing the results of different clinical screenings for probable bruxism and the establishment of an international standard for probable bruxism diagnosis will benefit the comparability of clinical trials in this field.

For the diagnosis of TMD, the DC/TMD, primarily established as RDC/TMD in 1992 and updated in 2014, can be regarded as the standard assessment and diagnostic tool [30]. For this reason, participants are examined and diagnosed following the guidelines of the DC/TMD in the present trial. Only pain-related TMDs are included in the trial as these conditions—but not pain-free intra-articular TMD—can be effectively managed by stabilization splints. These diagnoses are also used to discern the bruxism cohort, in which such a diagnosis led to exclusion. As an additional tool to assess trial eligibility, the GCPS is applied in the TMD cohort as a short, reliable, and valid instrument [38] for which a correlation with splint treatment effects was established [39]. Patients with GCPS grade III and IV are excluded since these scores point to high pain and moderate to severe disability that in most cases cannot be sufficiently alleviated by splint treatment and instead require multimodal pain therapy [39].

The bruxism and TMD cohort are then investigated for differences in OHRQoL and participant satisfaction with the splints in relation to their fabrication mode. OHRQoL was chosen as the primary outcome parameter, as OHRQoL with the splints determines participant compliance and thus the use of the splint, which consequently has an impact on the therapeutic efficacy and the technical outcome of the splint. The assessment of OHRQoL, therefore, forms the base for the future selection of treatment options enabling a maximum of treatment comfort and benefit for the patients [40]. For assessment of OHRQoL, the OHIP-G14 is used, which is an established questionnaire focusing on the evaluation of oral function, orofacial pain, orofacial appearance, and psychological impact [41–44]. To further integrate questions that specifically focus on participant satisfaction with the splints, participants are asked to rate wear comfort and retention of the splints on a Visual Analog Scale (VAS). Therapeutic efficacy and technical outcome are evaluated since these parameters determine clinical applicability as well as the service life of the splints and are therefore—in conjunction with OHRQoL—important measurements for the cost and benefit ratio. Especially for the GCPS, it was shown that it allows monitoring of even small changes in TMD symptoms [20] turning it into a sensitive instrument to validate therapeutic efficacy.

This trial will thus provide important information on key aspects of the clinical outcome of 3D printed stabilization splints that will benefit future individuals with bruxism and TMD and help dentists decide which fabrication method is preferable for a particular patient. However, since 3D printed splint materials show different mechanical properties like hardness, flexibility, and fracture toughness [45], the results of the present study may not be applicable to all types of 3D printed splints. The authors, therefore, hope to encourage further research in this field investigating the clinical outcomes of different 3D printed stabilization splints.

## Trial status

The protocol version 1.1 from the 22^nd^ of December 2023 was approved by the Ethics Committee of the Albert-Ludwigs-University, Freiburg, Germany, on the 18^th^ of January 2024. Recruitment began thereafter and is planned to be completed in September 2024.

